
### Work package 1 outputs

WP1 will provide evidence of the variation in the uptake of EPaCCS across the three regions in the UK and will identify factors associated with unequal EPaCCS access. The study will describe similarities and differences in the content and creation of EPaCCS which will inform the development of standardised EPaCCS in the future. We will work with key stakeholders (EPaCCS providers, ICBs and health professionals) and in close collaboration with local populations to ensure those who promote end-of-life care decision-making facilitated by EPaCCS are more accessible and acceptable to individuals across the social strata. This will also include bespoke training for health professionals in culturally competent and literate care to enable end-of-life care discussions and decision-making.

### Work package 2: evaluation of the effect of EPaCCS on place of death and secondary healthcare use at end of life and cost minimisation analysis of EPaCCS (objectives 2A and 2B)

The second work package will adopt a retrospective cohort design under a natural experiment framework to evaluate the effects of EPaCCS on quality indicators of end-of-life care. The quality indicators used in this work package include the place of death (primary outcome) and time spent in hospital in the last 90 days of life (secondary outcome).^48^ The hypothesis for work package 2 is that people with EPaCCS records are less likely to die in hospital and more likely to spend less time in hospital in the last 90 days of life compared with people without EPaCCS records. An EPaCCS record may address one or both sides of the cost-effectiveness ratio; reducing futile or unwanted treatments will save hospital resources while improving goal-concordant care realises more utility. However, there is also the potential for increased costs, notably through substitution effects, for example, if people die in a hospice instead of in a hospital. We therefore hypothesise that EPaCCS improve the cost-effectiveness of care near the end of life.

Using the CMC-WSIC linked dataset and the Leeds dataset, the study will use a natural experiment approach^33^ and establish cohorts of patients who have died having EPaCCS (case) or not having an EPaCCS (control) in each dataset separately. Place of death will be coded as a binary variable for individual-level analysis, indicating whether death occurred in a hospital or elsewhere. For ecological analysis, rates of hospital deaths per year will be calculated for each one of the eight health boroughs (previously called CCGs) in North West London. Time spent in hospital will be derived as a continuous variable measuring the number of days between admission and discharge within the last 90 days of life, or between admission and death for patients who died in hospitals. Rates of time spent in hospital within the last 90 days of life per year will also be calculated. The cost analysis will use the patient-level cost data available in WSIC. Formal costs will be estimated by combining utilisation frequencies in the data with unit costs for different services.^49^ Informal care hours will be estimated from the literature on end-of-life care populations and associated costs using the substitution method (primary analysis) and opportunity cost method (sensitivity analysis). Intervention costs will be estimated using NHS data.^50^ We will model costs after diagnostic testing of different modelling approaches in the context of distributional characteristics.^51^

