**Ethics and dissemination:**

Research approval has been secured from the Health Research Authority (ref 24/LO/0194), London - South East Research Ethics Committee (ref 24/LO/0194) and Confidentiality Advisory Group (ref 24/CAG/0046). Dissemination of findings will occur through peer-reviewed publications, knowledge exchange events and collaborative efforts with patient and public involvement partners.

STRENGTHS AND LIMITATIONS OF THIS STUDYInclusion of all Electronic Palliative Care Coordination Systems (EPaCCS) records in London (2010–2022), Leeds (2015–2023) and Bradford (2015–2023) with an additional cohort of patients without EPaCCs for Leeds (2021–2023) and London makes this the largest collection of data sources in an EPaCCS UK study.Following the ‘nothing about us without us’ philosophy, there is strong patient and public involvement collaboration at every stage of the project.A natural experiment aims to provide credible causal estimates of EPaCCS effects on end-of-life outcomes, which will strengthen the evidence base.Recommendations to key stakeholders based on the findings will inform future EPaCCS use.Challenges comparing EPaCCS due to the interoperability of the data may limit the generalisability of the findings to other EPaCCs within the UK.

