### Methods and analysis

### Study design

Objectives 1A–1C will be addressed using descriptive statistics, objectives 1D and 1E using multivariable regression and objectives 2A and 2B using a natural experiment framework, which will allow us ultimately to make conclusions and recommendations about the continued use of EPaCCS.^33 34^ Descriptive statistics and multivariable regression are key tools in quantitative end-of-life research where there is a high reliance on routine data.^35^ However, these methods are not always reliable for generating credible causal estimates of treatment effects.^36^ Provided underlying assumptions are met,^37^ natural experiments can generate causal evidence from observational data, including routinely collected data. These have been little used in end-of-life care research to date,^38^ but may be particularly impactful in a field where randomised trials are infrequent and methodologically challenging,^39^ reliance on routine data is paramount^40^ and selection bias in routine data is a persistent concern.^41^

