### Data sources

The study will use non-identifiable data from three EPaCCS across three distinct geographical locations in the UK, namely London, Leeds and Bradford, which combined have a population of 10.4 million people. These EPaCCS were introduced at different times within the same city and across different cities. This has led to natural variation in exposure, resulting in datasets that cover varying time periods: 2010–2022 in London, and 2015–2023 in Leeds and Bradford. Nonetheless, these EPaCCS are well established and contain a sufficient number of records, as illustrated in table 1, to enable meaningful individual site analyses and answer our research questions. Additional anonymised EPaCCS data from different regions will be considered if made available during the study. The sample size will be determined by the data available in the three datasets and will vary depending on the analysis.

**Table 1 T1:** EPaCCS and data availability

EPaCCS location	EPaCCS specific data
London EPaCCS	Coordinate My Care (CMC) served as the commissioned EPaCCS in London from 2010 to 2022, during which time it was also the largest UK EPaCCS. Covering 32 CCGs serving a population of 8.9 million, this EPaCCS dataset reflects a diverse urban patient population in terms of diagnosis, ethnicity and socioeconomic background. CMC records comprise data from various healthcare settings, including primary and secondary care, hospices and nursing homes. The dataset encompasses demographics, diagnoses, care preferences, the ceiling of treatment, resuscitation status, living circumstances, prognosis, performance status, date and place of death. Additionally, data is available regarding how often the record was accessed by urgent and non-urgent healthcare workers. In later years, patients had the option of starting a ‘MyCMC’ plan, whereby they use a patient portal to input some data themselves. The anticipated numbers for inclusion in the dataset are 140 000 records, of which 100 000 are for deceased patients.

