Leeds EPaCCS	The Leeds EPaCCS dataset represents a combined dataset from community palliative care providers that includes all primary care practices and two city hospice sites (St Gemma’s Hospice and Wheatfields Hospice) and limited secondary care data (eg, unplanned hospital admissions in the last 90 days of life). This dataset encompasses decedent patient records spanning from 2015 to 2023. It includes linked healthcare records data including primary and secondary care data, such as hospital admissions and diagnosis of severe mental illness or learning disability. The EPaCCS in Leeds covers the entirety of the former Leeds CCG serving a population of around 870 000 people through 94 general practitioners (GP) practices. Since 2019, approximately 50% of all people who die in Leeds have an EPaCCS.^67^ Data for all deaths across Leeds from 2021 to 2023 are also available, including decedents without EPaCCS. This will enable comparative analysis between patients with or without EPaCCS records. The anticipated number of records for inclusion is 15 500 decedent records.
Bradford EPaCCS	The Bradford EPaCCS dataset is collected and shared among healthcare providers (including both NHS and voluntary sector providers) through electronic health records. This dataset includes decedent patient records spanning from 2015 to 2023. This EPaCCS is commissioned across the Bradford and Airedale districts, serving a combined population of 585 000 with approximately 4800 deaths per year. Approximately 48% of all deaths in this area had an EPaCCS record in 2018/19.^68^ The anticipated number of records for inclusion is 17 000 decedent records.

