### Creating comparative cohorts

This study will take an inclusive approach to defining the cohorts for inclusion in the individual-level analysis, identifying deceased patients who had mention of one of the four main disease-related causes of death in their clinical records within the last year of life (cancer, dementia, heart or lung disease). Based on previous analyses^52^ and publicly available national data,^53^ we hypothesise that 22–30% of the EPaCCS cohort will die in the hospital compared with 45–50% in the non-EPaCCS group. The inverse probability of treatment weighting will be used to account for the confounding resulting from the non-random allocation of EPaCCS to the groups and balance characteristics between cohorts.^54^ First, a multivariable logistic regression will be used to determine the propensity score weights. Factors included in the model to estimate propensity scores will include the confounders selected to be included in the main outcome analysis (such as age, sex, ethnicity, deprivation and primary diagnosis). These confounders will be cautiously selected based on thorough discussions with our team, which includes experts in palliative care, input from the patient and public involvement group with lived experience in end-of-life care, and a comprehensive literature search. Then, for each patient inpatient encounter, a weight defined as the inverse of the probability of the treatment they had received will be calculated. The balance of patients’ characteristics will be assessed visually and by examining the standardised mean differences.^55^

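### WP2 is labelled a natural experiment, but the individual-level analyses in both datasets, and all that is described for Leeds, are adjusted record-versus-no-record comparisons that do not use the staggered roll-out

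*Protocol article*

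**What the plan says.** The Study design section assigns objectives 1D and 1E to multivariable regression and 2A and 2B to a natural experiment. Of descriptive statistics and regression it says that "these methods are not always reliable for generating credible causal estimates of treatment effects". Subject to assumptions being met, it says that "natural experiments can generate causal evidence from observational data, including routinely collected data", and it gives selection bias in routine data as a continuing worry in this field. The strengths and limitations box says: "A natural experiment aims to provide credible causal estimates of EPaCCS effects on end-of-life outcomes".

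The variation is described under Data sources: "These EPaCCS were introduced at different times within the same city and across different cities". The next sentence there says that this produced natural variation in exposure.

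The Work package 2 section applies the natural-experiment approach to the linked North West London data and to the Leeds data, and will "establish cohorts of patients who have died having EPaCCS (case) or not having an EPaCCS (control) in each dataset separately". Under Creating comparative cohorts, "The inverse probability of treatment weighting will be used to account for the confounding resulting from the non-random allocation of EPaCCS to the groups". The propensity factors are confounders "such as age, sex, ethnicity, deprivation and primary diagnosis". The Individual patient-level analyses section adds mixed effects logistic regression with further covariates, including carers, living circumstances, place of care and comorbidity. Timing enters as season or financial quarter.

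The ecological analysis is planned for the eight North West London boroughs only. It relates the yearly proportion of deaths with a record to yearly hospital-death and hospital-time rates.

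For Leeds, Table 1 says that decedents without a record are available for 2021–2023, that the system covers the whole former CCG (94 practices), and: "Since 2019, approximately 50% of all people who die in Leeds have an EPaCCS".

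**The concern.** A natural experiment earns a causal reading because something outside the patient's and clinician's control, such as when a system went live locally, determines exposure. Holding one's own record is not of that kind. It plausibly depends on being recognised as approaching death and on willingness to plan, and both plausibly affect where a person dies.

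Weighting and regression remove only the part of that selection carried by measured covariates. The individual-level estimates would thus have the weakness that the Study design section attributes to regression, under a label that suggests otherwise.

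At stake is what the study may conclude. Its findings are to support recommendations on continued use of EPaCCS. A Leeds odds ratio, or an individual-level London odds ratio or cost difference, presented as natural-experiment evidence would carry more weight than its design supports.

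**Working it through.** **1. Where exposure variation comes from in each WP2 analysis**

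| Analysis | Exposure contrast | Role of roll-out |
|---|---|---|
| North West London, individual level (2A) | own record vs none | season/financial quarter as a covariate |
| North West London, costs (2B) | own record vs none | no roll-out contrast described |
| Leeds, individual level (2A only) | own record vs none, 2021–2023 | as for London 2A; no roll-out contrast described |
| North West London, ecological (2A) | proportion of deaths with a record, by borough and year | used indirectly, through achieved uptake |

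At individual level no introduction date, instrument, difference-in-differences or pre-introduction comparison is named. The Leeds window opens in 2021, after uptake had been about 50% city-wide since 2019. Variation between the 94 practices is not described.

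The ecological analysis has eight boroughs. With 13 years of the London register (2010–2022) or 14 years of deaths (2010–2023), that is at most 8 × 13 = 104 or 8 × 14 = 112 borough-years. Its exposure is realised uptake rather than an external start date. Its description names no calendar-year term, so a shared time trend in uptake and place of death is not visibly separated from an effect.

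**2. The contrast the protocol expects**

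The protocol states no power or sample size figure to reproduce. Its hypothesised hospital-death rates are 22–30% with a record and 45–50% without.
- Risk difference: 45 − 30 = 15 points to 50 − 22 = 28 points.
- Risk ratio: 0.30/0.45 = 0.67 to 0.22/0.50 = 0.44.
- Odds ratio: (0.30/0.70)/(0.45/0.55) = 0.52 to (0.22/0.78)/(0.50/0.50) = 0.28.
- E-value, R + √(R(R − 1)) with R the inverted risk ratio: 2.37 for R = 1.50 and 3.97 for R = 2.27. An unmeasured factor would need a risk ratio of at least this size with both record-holding and hospital death, beyond measured covariates, to explain the whole contrast.

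**3. Illustration with no true effect**

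Let U be a binary factor that the weights do not capture. With h₁ and h₀ the hospital-death risks with and without U, and u the prevalence of U in a group, the group's rate is u·h₁ + (1 − u)·h₀. Every value of u and h is assumed; none comes from the document.

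| h₁, h₀ | U in record / no-record group | Hospital death, record | Hospital death, no record | OR |
|---|---|---|---|---|
| 20%, 60% | 90% / 30% | 24% | 48% | 0.34 |
| 20%, 60% | 80% / 30% | 28% | 48% | 0.42 |
| 20%, 55% | 70% / 30% | 30.5% | 44.5% | 0.55 |
| 25%, 55% | 70% / 40% | 34% | 43% | 0.68 |
| 20%, 55% | 60% / 40% | 34% | 41% | 0.74 |

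Second row worked: 0.8 × 0.20 + 0.2 × 0.60 = 0.28; 0.3 × 0.20 + 0.7 × 0.60 = 0.48; (0.28/0.72)/(0.48/0.52) = 0.42.

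The top two rows fall inside the hypothesised ranges. The lower rows give gaps of 7 to 14 points, short of the expected 15 to 28.

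**The case against.** The authors can say that they hedge. The causal claim is conditional on assumptions, the strengths box states an aim, and the objectives are to explore effects. Non-random allocation is acknowledged openly. The Sensitivity analysis section says that techniques for unobserved confounding will be considered, and a full statistical analysis plan is promised. The Study design section calls regression not always reliable, rather than unreliable, and does not mention weighting. All of this stands, and it softens the point. It does not give the individual-level contrast a source of exposure variation outside patient and clinician choice.

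Three stronger readings are tempting and are not supported:
- **That WP2 as a whole lacks any natural-experiment element.** The ecological analysis uses uptake by borough and year, and its section leaves room for other approaches. It is limited, but not absent.
- **That Leeds contains no roll-out variation.** The article gives a city-wide figure and is silent on practices. It supports only the statement that no roll-out analysis is described there.
- **That the wish to avoid hospital is recorded only in EPaCCS, so weighting cannot balance it.** The linked dataset holds coded primary, secondary, community and social care data. Whether preferences or markers of recognised dying appear in it is not stated.

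It is also fair to say that the illustration shows bias to be possible without measuring it, and that it describes only what remains after weighting.

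**Conclusion.** The point holds as a mismatch between label and method. The individual-level analyses in both datasets, and everything described for Leeds, are adjusted observational comparisons that rely on no unmeasured confounding and do not use the staggered introduction the protocol cites. The article states exposure, weighting and model, so this is not detail left to the analysis plan. The Leeds part bears on 2A alone, because 2B uses only the linked London data.

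The size of any bias is unknown. Under the assumed values above, residual selection could account for part or all of the hypothesised contrast, depending on how much the measured covariates capture. The consequence lies in the strength of the conclusions: the analyses can be run as planned, but their results should not be presented as natural-experiment evidence.

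**What to change.** 1. Confine natural-experiment and causal wording to analyses that use roll-out variation. Report the individual-level record-versus-no-record results in North West London (2A and 2B) and all of Leeds 2A as adjusted associations. State the no-unmeasured-confounding assumption beside each, and carry that limit into the recommendations. This needs no new data or model. The cost is a weaker stated conclusion for Leeds and for the individual-level London estimates.

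2. Optionally, if borough or practice introduction dates and a pre-introduction period prove to be available in the linked London data, add a supplementary analysis. Classify every decedent by whether EPaCCS was available locally before death, whether or not they held a record, with borough and calendar-period effects. Report it as the effect of system availability, which is a different estimand from the effect of holding a record. Feasibility is not established: the London system and the death records both start in 2010 and no local start dates are given. With eight boroughs, the interval for any roll-out contrast is likely to be wide.

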North West London dataset	CMC records will be linked with the ‘Whole Systems Integrated Care’ (WSIC) dataset. WSIC is an electronic record used by healthcare professionals in North West London, which has a population of 2.4 million, to document essential information about patient care in the region (eight health boroughs, previously defined as CCGs).^65^ The WSIC dataset will include all individuals who have died in North West London within the timeframe spanning from 2010 to 2023. This linkage will allow the creation of two cohorts for comparison: individuals with EPaCCS (CMC) and those without EPaCCS. All decedents with a CMC record within the WSIC catchment area will be identified for inclusion within the linked dataset, while decedents without such records will form the control group. The WSIC dataset includes coded primary, secondary, acute, mental health, community health and social care data. This dataset also includes detailed information on social determinants of health, including ethnicity, and mortality data, including place of death. Cost data is also available as patient-level costs referring to the indicative spend calculated separately for each patient for each healthcare sector. This will be used in a cost minimisation analysis of EPaCCS, and it includes primary care level, acute, community, mental health and social care costs. Data linkage will be carried out by North West London Integrated Care Board and supported by existing data sharing framework.^66^ Figure 1 illustrates the data flow and linkage process. The linked dataset will be de-identified prior to being made available to the research team for the analysis

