The study will describe how EPaCCS are used, specifically who creates EPaCCS records and what information they encompass regarding individuals’ preferences for end-of-life care. The study will describe data fields across each of the three datasets and evaluate their completeness. Additionally, a descriptive analysis of the three EPaCCS datasets will be undertaken to describe the creation and content of the records across the three regions. These specific regions were chosen for being large metropolitan areas with varied levels of material deprivation and a high concentration of ethnic minority groups. This analysis will focus on the elements of ACP used to support decision-making at the end of life, which include documentation of the ceiling of treatment, resuscitation status, preferred place of care and preferred place of death. The study will also explore if changes are made to decision-making over time for each of these elements. As the three EPaCCS in the study contain data from different periods in time, we will take into account the different timescales during the analyses. The uptake of EPaCCS will be evaluated by describing the number of records created across different time periods and locations. The study will also investigate the setting of the initial record creation (hospital care, primary care, community care). Furthermore, the study will describe the clinical characteristics of patients such as their diagnosis, performance status, capacity for decision-making, living arrangements and expected prognosis. The study will also describe their socio-demographic characteristics with a particular emphasis on social determinants of health such as age, gender, socioeconomic position and ethnicity. The socioeconomic position will be defined using the Index of Multiple Deprivation (IMD), a standard scoring system based on a range of economic, social and housing data, creating a single deprivation score for each small area of the country. Using methodology previously employed in studies by the research team,^43 44^ an IMD score will be created for each patient based on their postcode which will reflect the deprivation data for the Lower-layer Super Output Area (LSOA) within which the postcode falls. Moreover, the study will investigate across sites the association between social determinants of health and the completion of each of the four previously mentioned ACP elements. Table 2 shows the mapping of the study objectives to data sources and eligibility criteria. Exclusion criteria for all data sources are participants who have chosen National Data Opt-Out and those who have withdrawn consent.

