
**Table 2 T2:** Mapping study objectives to data sources and eligibility to be included in analyses

Objectives		Data sources and eligibility
Work package 1		
1A	To describe and categorise the data fields and completeness of data contained within each EPaCCS register.	Anonymised EPaCCS data from London (CMC, n=140 000), Leeds (n=15 500) and Bradford (n=17 000)
1B	To describe the creation and content of EPaCCS records and elements relating to end-of-life decision-making preferences and ACP (ceiling of treatment, preferred place of care, and death and resuscitation status) in different regions across England.	
1C	To describe the socio-demographic and clinical characteristics of individuals who have created EPaCCS records in different regions across England.	
1D	To estimate associations between social determinants of health (socioeconomic position, ethnicity, age, and gender) and the completion of elements of ACP within EPaCCS.	
1E	To estimate associations between social determinants of health (socioeconomic position, ethnicity, age, and gender) and the creation of EPaCCS.	WSIC-CMC dataset of North West London deceased patients with/without EPaCCSLeeds decedent dataset 2021–2023 of deceased patients with/without EPaCCS
Work package 2		
2A	To explore the effect of EPaCCS on place of death and hospital use in the last 90 days of life.	WSIC-CMC dataset of North West London deceased patients with/without EPaCCSLeeds decedent dataset 2021–2023 of deceased patients with/without EPaCCS
2B	To explore the effect of an EPaCCS record on healthcare costs in the last 90 days of life.	WSIC-CMC dataset of North West London deceased patients with/without EPaCCS

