### Ecological analysis

Treating the regions covered within the North West London ICBs as a random effect, mixed effects regression will be used to examine the effect of the rate of patients who died having EPaCCS on the annual rates of hospital deaths and time spent in hospital within the last 90 days of life, calculated, respectively, as the number of deaths with EPaCCS over total deaths, the number of in-hospital deaths over total deaths, and the aggregate time spent in hospital within the last 90 days of life over total deaths.^56^ Other approaches will be considered upon examining the data and the annual number of patients who died having EPaCCS.^33^

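### Exposure in work package 2 is having a record at death, whenever it was made, while hospital days and costs cover the whole last 90 days; records made inside that window can bias the comparison, with a sign and size the protocol does not allow one to predict

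*Protocol article*

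**What the plan says.** The Work package 2 section sets the individual-level exposure by status at death: the study will "establish cohorts of patients who have died having EPaCCS (case) or not having an EPaCCS (control) in each dataset separately". Table 1, under the North West London dataset, agrees: "All decedents with a CMC record within the WSIC catchment area will be identified for inclusion within the linked dataset", and decedents without a record become controls. The Ecological analysis section uses the same definition for its exposure rate, "the number of deaths with EPaCCS over total deaths".

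The outcomes are as follows.
- Primary: "Place of death will be coded as a binary variable for individual-level analysis, indicating whether death occurred in a hospital or elsewhere".
- Secondary: time in hospital, "measuring the number of days between admission and discharge within the last 90 days of life", or from admission to death for those who die there.
- Costs, objective 2B: "To explore the effect of an EPaCCS record on healthcare costs in the last 90 days of life".

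Work package 1 will describe "the setting of the initial record creation (hospital care, primary care, community care"), so all three are treated as possible origins of a record.

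The propensity model (Creating comparative cohorts) gives demographic factors, deprivation and main diagnosis as examples of confounders. The outcome model (Individual patient-level analyses) adds carer, household, place-of-care and comorbidity variables and a season or financial-quarter term. The Sensitivity analysis section promises to vary how cohorts are identified, without naming a timing rule. Its COVID-19 exclusion depends on calendar period.

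**The concern.** The exposure can begin after the outcome has started to accrue. Someone whose record is made on day -5 counts as exposed for all 90 days, although 85 of them came before the record. Hospital use and costs on those days cannot have been caused by the record, yet they enter the EPaCCS arm.

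The second problem is selection, and it reaches place of death too. Whether a person acquires a record in the last weeks may depend on being at home, being discharged, or being on a ward where staff create one. The course that leads to the outcome then helps to decide exposure. The variables named for weighting are baseline characteristics. Balancing them does not align the start of exposure with the start of the outcome window, and calendar quarter says nothing about time from record to death.

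The primary outcome, the secondary outcome and the cost comparison all rest on this exposure definition, in a study that presents its natural experiment as a source of credible causal estimates.

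**Working it through.** **1. What the protocol supplies.** There is no creation-to-death distribution and no power calculation, so there is no planned figure to reproduce. For scale, the Creating comparative cohorts section expects 22–30% hospital deaths with EPaCCS and 45–50% without. With OR = [p1/(1−p1)] / [p0/(1−p0)]:
- 22% v 50%: 0.282/1.000 = 0.28
- 30% v 45%: 0.429/0.818 = 0.52

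**2. Null simulation.** The question is what the ever-record rule returns when EPaCCS has no effect. Every input here is assumed, because the protocol gives none.
- 200,000 decedents per scenario, 90 daily steps ending in death (d counts the steps from 0), 8% in hospital at the start.
- Daily admission probability 0.012 × [1 + 3(d/90)³]; daily discharge probability 0.10 × [1 − 0.7(d/90)³].
- 25% hold a record before the window, independent of everything else.
- Daily probability of creating a record inside the window: (A) 0.006 whatever the hospital status; (B) 0.008 out of hospital, 0.001 in; (C) 0.003, rising to 0.4 on the day of discharge; (D) 0.003 out, 0.02 in.

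The resulting coverage is 55–64% of deaths, and 55–61% of records fall inside the window.

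| Late creation | Hospital death, ever v never | OR | Mean hospital days |
|---|---|---|---|
| A independent of status | 43.3% v 43.0% | 1.01 | 15.9 v 15.7 |
| B mainly in the community | 41.6% v 44.7% | 0.88 | 14.7 v 17.1 |
| C triggered at discharge | 41.4% v 45.6% | 0.84 | 17.2 v 13.2 |
| D during admission | 46.1% v 38.9% | 1.34 | 18.0 v 12.8 |

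In C the two outcomes move in opposite directions: the rule favours EPaCCS on place of death and disfavours it on days. Varying the early share in C from 5% to 45% gives OR 0.83–0.85. With no late records at all, OR is 1.00 and days are 15.8 v 15.7. Costs were not simulated; their hospital component would follow the days.

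Other assumed hazards widen the range. Community-only creation with 80% of records late gave OR 0.66, and one in-hospital variant gave 1.61.

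**3. Which comparison group removes the bias.** Same runs, exposed = record before the window:

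| | v never recorded | v all without a record by day -90 |
|---|---|---|
| B | 42.6% v 44.7%, OR 0.92 | 42.6% v 43.0%, OR 0.98 |
| C | 43.0% v 45.6%, OR 0.90 | 43.0% v 42.9%, OR 1.00 |
| D | 42.5% v 38.9%, OR 1.16 | 42.5% v 43.0%, OR 0.98 |

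Simulation error on log OR for the right-hand column is about 1/√(200,000 × 0.43 × 0.57 × 0.25 × 0.75) = 0.01, so 0.98 is compatible with no effect. Mean days there are equal to the first decimal (15.7 v 15.7 in B and D, 15.8 v 15.8 in C). Dropping later-recorded decedents from the controls keeps part of the bias, because controls are then chosen on what happened after day -90.

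**4. What the landmark costs.** Suppose the whole 30% v 45% contrast were causal, coverage were 50% (Table 1, Leeds) and 55% of records were late (assumed). Then 22.5% of decedents are early, 27.5% late and 50% never recorded. The landmark comparison group has (0.275 × 30% + 0.50 × 45%)/0.775 = 39.7% hospital deaths. The OR becomes 0.429/(0.397/0.603) = 0.65 instead of 0.52.

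**The case against.** The best defence has four parts.

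First, the definition alone does not create bias under the null. Scenario A shows none, so creation must depend on hospital status or trajectory. That stands. The dependence is plausible given the three creation settings, but the protocol does not establish it.

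Second, a reader might infer that the hospital-death bias must favour EPaCCS, because people who die quickly in hospital miss the chance of a record. The protocol does not support that. It lists hospital care among the creation settings, and creation during admission pushes the odds ratio above 1. A reader might also infer that the artefact explains the expected contrast. None of the simulated values reaches 0.28–0.52, and all rest on assumed hazards.

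Third, for place of death a record made after day -90 still precedes the outcome and may affect it. The landmark answers a different question, at the price shown in step 4. This stands, and it is why the ever-record contrast should not be relegated to description for that outcome.

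Fourth, the confounder lists are only examples, cohort identification will be varied in sensitivity analyses, and a full analysis plan is promised. A timing rule could be added there. But the point is not a missing detail: the protocol states an exposure rule, and following it as written credits earlier hospital use to a later record.

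**Conclusion.** The concern holds in conditional form. The text is clear that exposure is fixed at death with no timing condition, while days and costs look back over 90 days; care before a late record is therefore misattributed by construction. Bias under no effect, for all three outcomes, further requires that late creation depends on hospital status or dying trajectory. Neither sign nor size can be derived from the protocol. In the main simulated scenarios the null hospital-death OR ran from 0.84 to 1.34 and the difference in days from 14.7 − 17.1 = −2.4 to 18.0 − 12.8 = +5.2. These figures show that the effect can matter and can go either way; they are not estimates for London or Leeds. The share of late records and where they were made decide the real size. Neither the weighting nor the calendar term, as described, deals with it.

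**What to change.** Settle the following in the protocol or analysis plan before work package 2 is run.

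- **Hospital days and costs:** make the primary contrast a record created on or before day -90 against all decedents with no record by day -90. Keep those who acquire a record later in the comparison group. Alternatively, give controls matched index dates with the same hospital status at index as their cases, and count use and costs only from index to death.
- **Place of death:** report the same landmark or matched-index analysis beside the ever-record contrast, and do not interpret the ever-record contrast alone as causal.
- **Both:** report the distribution of time from record creation to death.

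The work is wording and some programming. Creation dates appear to be held already, since work package 1 counts records by period and the COVID-19 analysis identifies records by when they were made; confirm this for the Leeds decedent data. The price is fewer exposed decedents and dilution by later records, because the landmark estimates the effect of having a record by day -90, not of ever having one.
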